**[name]**

Globally, cardiovascular disease (CVD) was responsible for 17.5 million deaths, accounting for 46.2% of non-communicable diseases (NCDs) deaths. In Ghana CVDs has been the leading cause of death since 2001. The prevalence of CVD risk factors among adolescents and adults in Ghana has been increasing. The main aim of this study is to develop, implement and evaluate the effectiveness of a behavioral modification intervention program to reduce cardiovascular disease risk factors among secondary school students in Brong Ahafo, Ghana. The study will be a single blind cluster randomized controlled trial. Baseline data will be collected from 848 students after which schools will evenly be randomized using block randomization (1:1 ratio) of two digit blocks (A and B). School-based intervention will be implemented using the Information- Motivation-Behavioral skills (IMB) model to reduce CVD risk factors over a period of six months with pre and post intervention evaluations. The intervention module will be a health education and physical activity modules in the intervention schools. The control schools will go on with their normal school curriculum and will be waitlisted for similar intervention after the study. Follow-up data using same questionnaire will be collected within two weeks after the intervention is completed. The primary outcomes are knowledge, motivation, behavioral skills, physical activity, smoking, alcohol, dietary intake, while weight, body mass index, and blood pressure were secondary outcomes. Weight, height and blood pressure will be measured using standardized equipment by trained health staff. Intention-to-treat analysis will be performed after replacing missing values using multiple imputation method. The generalized linear mixed model (GLMM) will be used to test the effect of group, time and group-time interactions after controlling for potential confounders.

The study is expected to improve knowledge, motivation, behavioral skills, physical activity, and healthy eating habits among students in the intervention group. The study is also expected to reduce weight, BMI, smoking and alcohol habits of the intervention group.

i

**LIST OF ABBREVIATIONS**

BMI Body Mass Index

CDC Centre for Disease Control and Prevention

CHD Coronary Heart Disease

CONSORT Consolidated Standards of Reporting Trials

CVD Cardiovascular Disease

DALY Disability Adjusted Life Years

DBP Diastolic Blood Pressure

GDHS Ghana Demographic and Health Survey

GHS

GLMM

Ghana Health Service

Generalized Linear Mixed Model

GSS Ghana Statistical Service

IMB

IOM

Information-Motivation-Behavioral Skills

Institute of Medicine

ITT

MCAR

Intention-To-Treat

Missing Completely At Random

MOE Ministry of Education

MOH Ministry of Health

MVPA Moderate to Vigorous Physical Activity

NCD Non Communicable Disease

PA Physical Activity

PACTR

PAQ-A

Pan African Clinical Trials Registry

Physical Activity Questionnaire for Adolescents

PTA RCT

Parent Teacher Association

Randomized Controlled field Trial

SBP Systolic Blood Pressure WHF World Heart Federation WHO World Health Organization

viii

**CHAPTER 1**

**INTRODUCTION**

**1.1 Background**

Non communicable diseases (NCDs) are the number one public health challenge of the 21st century. There were 56 million worldwide deaths in 2012 where 38 million deaths representing 68% were caused by NCDs. More than 40% (16 million) of NCD deaths occur prematurely, affecting people below 70 years. Almost three quarters of all NCD deaths accounting for 28 million and majority of premature deaths, 82%, occurred in developing countries where most of the world’s population lives (WHO,

2011a; 2014). By 2020, NCD deaths are projected to almost equal the combined deaths from communicable, perinatal, maternal, and nutritional diseases in the African continent and to exceed the combined deaths by 2030 (WHO, 2011a). The NCDs are mainly cardiovascular diseases (CVDs), cancers, chronic respiratory diseases and diabetes (Hunter & Reddy, 2013; WHO, 2015a). Cardiovascular deaths accounts for almost half (46.2%) of all NCD deaths, followed by cancer deaths, 21.7%, with respiratory diseases causing 10.7%, and diabetes with 4% deaths (WHO*,* 2014).

Cardiovascular diseases caused more deaths annually than any other causes (Mozaffarian et al., 2015; WHO, 2015b; World Heart Federation, 2015; Smith et al., 2012). Globally, an estimated 17.5 million people died in 2012 due to CVDs, representing 31% of all global deaths (WHO, 2015b) and affected a third of adult population in the world making it the largest epidemic ever known to mankind (Yusuf, Wood, Ralston, & Reddy, 2015). In Ghana, cardiovascular diseases have been the

leading causes of all NCDs and hospital deaths in 2008 accounting for 14.5% of total deaths (Bosu, 2013). According to the Ghana Health Service (GHS, 2015), CVDs are

the leading causes of NCD deaths with an estimated 35,000 deaths per year. In a five-year review of autopsy cases (19,289) from 2006 to 2010 in one of the teaching hospitals in Ghana (Korle-Bu Teaching Hospital, KBTH) found out that more than one-fifth (22.2%) of the deaths were due to CVDs (Sanuade, Anarfi, Aikins, & Koram,

2014). Also CVDs rose from the seventh and tenth causes of death in the capital

(Accra) in 1953 and 1966 respectively to the number one cause of death in 1991 and

2001 and has continued as one of the major causes of death since then (Agyei-Mensah

& de-Graft Aikins, 2010). In 2014, stroke and coronary heart disease (CHD) were ranked as the 2nd and 4th leading causes of death in Ghana accounting for 9.75% and

6.48% of all deaths respectively (World Health Rankings, 2014). The WHO (2015c) has reported that NCDs accounted for 34% of total deaths and 31% disability adjusted life years in Ghana with CVDs being the leading cause of NCD deaths.

Risk factors of CVDs are of two types which are modifiable and non-modifiable factors. Non-modifiable risk factors include advancing age, male gender, black race– ethnic background, prior stroke/transient ischemic attack or history of coronary heart disease and family history of stroke. On the other hand, modifiable risk factors of

CVDs include physical inactivity, smoking, alcohol consumption, unhealthy diet, obesity, hypertension, and diabetes mellitus (World Heart Federation, 2017).

Physical inactivity is the fourth leading risk factor for mortality (WHO, 2010). An estimated 3.2 million deaths occur each year due to physical inactivity. In 2010, prevalence levels of physical inactivity in the Eastern Mediterranean region was the highest (88%) followed by both Africa (85%) and Western Pacific regions (85%). In

2010 globally, 23% of adults aged 18years were physically inactive as explained by doing less than 150 moderate-intensity physical activity per week or its equivalent (WHO, 2014). On the other hand, 81% adolescents between the ages of 11-17 years were physically inactive in 2010 as explained by doing less than 60 minutes of moderate to vigorous daily physical activity, as recommended by the WHO (WHO,

2014). People who are physically inactive have a greater risk for all-cause mortality as compared to those who do at least 30 minutes moderate physical activity on most days in the week. Engaging in 150 minutes of moderate physical activity each week reduces the risk of coronary heart diseases, stroke, hypertension, diabetes, depression, and cancers. Physical activity is a major determinant of energy expenditure and therefore fundamental to balance and weight control (WHO, 2010). A nationwide school based survey among adolescents in Ghana found out that proportion of secondary school students who reported being physically active all days for a total of at least 60 minutes per day during the past seven days were only 18.7% (MOH, 2012).

Tobacco use is one of the main causes of preventable deaths worldwide. Tobacco use is associated with cardiovascular diseases. There are currently about one billion smokers in the world. An estimated six trillion cigarettes are smoked annually by current smokers. Six million people die each year from tobacco use and exposure (WHO, 2011a). The GHS (2017a) reported that the prevalence of tobacco use in Ghana in 2014 was 5.1% among males and 0.4% for females. A research conducted among students of 11-17 years in Ghana revealed that prevalence of smoking among boys was 2.4% while girl smokers was 1.4% (Mamudu & Veeranki, 2013).

Alcohol consumption is associated with the risk of hypertension and hemorrhagic stroke. Globally, an estimated 3.3 million people died (5.9% of all worldwide deaths) in 2012 as a result of alcohol consumption. More than half of these deaths resulted in NCDs of which CVDs and diabetes accounted for 33% of these deaths. Globally, the levels of alcohol consumption in 2010 was estimated at 6.2 liters of pure alcohol per person ≥15 years of age (WHO, 2014). In Ghana, the levels of alcohol consumption in 2016 per person ≥15 years of age was estimated to be 2.7 liters (WHO, 2018a). In a research among 1,311 adolescents school students in Ghana found that prevalence of alcohol use among students was 42.3% (Hormenu, Hagan, & Schack, 2018).

Unhealthy diet accounts for 1.7 million deaths and 16 million DALYs worldwide as a result of low consumption of fruits and vegetables (WHO, 2014). Adequate fruits and vegetables intake reduces the risk of CVDs (Boeing et al., 2012). Consumption of high energy foods including processed foods like fats and sugars results in obesity (Mendonca et al., 2016). Also, high salt intake increases the risk of hypertension and

CVDs. Globally, the WHO has estimated that people consume between 9-12 g/day of salt which is far above the recommended intake of less than 5g/day. The WHO further indicated that saturated fat predisposes an individual to the risk of coronary heart diseases whereas monounsaturated and polyunsaturated reduces the risk (WHO, 2011a) while the consumption of fish is very low. A study in Ghana among secondary school students revealed the consumption of sweet snacks, sodas, and energy dense foods were high (Amoh & Appiah-Brempong, 2017).

Obesity has been a major problem in recent times. Globally, the prevalence of this risk factor has more than doubled since 1980 and 2014. There were 11% males and 15% females aged 18 years and older who were obese globally in 2014 (WHO, 2014). Thus half a billion adults worldwide are obese. Obesity is a major risk factor of diabetes, hypertension, coronary heart disease and stroke. Overweight and obesity are defined as BMI ≥25kg/m2 and ≥30kg/m2 respectively accounted for 3.4 million deaths in 2010 and 93.6 million Disability Adjusted Life Years (DALYs) (Cawley, Meyerhoefer, Biener, Hammer, & Wintfeld, 2015; WHO, 2014). The prevalence of childhood obesity is becoming a major challenge especially in low and middle income countries. This is as a result of overindulgence in consumption of high caloric foods, activities such as watching television, playing video games and the internet and other forms of physical inactivity (WHO, 2014). A nationwide study among secondary school students in Ghana reported that 8% of the students were either overweight or obese (MOH, 2012).

Hypertension is a major CVD risk factor (Chiolero, Bovet, & Paradis, 2013; WHO,

2014). The global prevalence of hypertension which is defined as systolic and/or diastolic blood pressure of ≥140/90 mmHg in adults aged ≥ 18 years was around 22% in 2014. The highest prevalence of hypertension across the WHO regions is in Africa, at 30% with the lowest prevalence in the region of the Americas at 18% (WHO, 2014). An estimate of 9.4 million people died worldwide in 2010 as a result of hypertension. The prevalence of hypertension in Ghana is about 48% as reported by the GHS (2017b) and has consistently ranked among the top ten causes of outpatient morbidity, admission, and death. The research was carried out in Ghana among 201 youth from three communities between the ages of 12-24 years found that 32.3% and 4% were pre-hypertensive and hypertensive respectively (Afrifa-Anane, Agyemang, Codjoe, Ogedegbe, & de-Graft Aikins, 2015).

The prevalence of diabetes has been increasing globally especially in low and middle income countries. This increase is largely due to modifiable risk factors such as physical inactivity, overweight, and obesity. The global prevalence of diabetes (defined as a fasting plasma glucose value ≥ 7.0mmol/L (126 mg/dl) or being on medication for raised blood sugar was estimated to be 9% in 2014. In 2012, diabetes killed 1.5 million people and 89 million DALYs (WHO*,* 2014). The prevalence of adult diabetes in Ghana is about 9% (GHS, 2017b).

Studies have shown that the risk factors for coronary heart disease and stroke begin in childhood that develops in adulthood (Juonala et al., 2010). This means that modifying risks factors and changing behavioral lifestyle for CVD should begin at the youthful age. Therefore, prevention of CVDs should be tackled right from an early age. Unfortunately, many people are not aware of CVD and its risk factors (Lao, Chan, Tong, & Chang, 2015) and because of this the disease burden keeps on rising. Also, merely educating the general public on CVD and its risk factors seems not to have achieved much. Therefore, adding intervention programmes to education especially for the youth on an ongoing process will equip them in protecting themselves from developing CVD disease in adulthood. Educating those who have already developed the disease should be ongoing so that they take the necessary steps in keeping the disease at its lowest levels and educate their families on the dangers of CVDs and its risk factors especially the youth.

School health interventions programmes have been shown to give consistent improvement on the general health status of students (Adab et al., 2015; He et al.,

2015) and that they are ideal places for health programmes (Khambalia, Dickinson, Hardey, Gill, & Baur, 2012; Ploeg, Maximova, McGavock, Davis, & Veugelers,

2014). The WHO (2011b) estimated that these modifiable risk factors cause 80% of

CVDs mainly physical inactivity, smoking, alcohol use, and unhealthy diet. Although cardiovascular diseases occur in middle and adult ages, the risk factors that cause the disease are mainly lifestyle behaviors that are learned during childhood and carried into adulthood.

Some behavioral studies have shown to result in some improvement in reducing the risk factors of CVDs. A school-based intervention to improve physical activity among secondary school students showed a statistically significant increase among the intervention group than the control group (Wang & Wang, 2018). A randomized control trial study was conducted to lower the intake of salt in students. The study found out that salt intake had decreased significantly in the intervention group and increased in the control group. The mean effect for intervention compared to the control group was -1.9 g/day (95% CI, -2.6 to -1.3 g/day; *p* < 0.001). Further, the systolic blood pressure showed a mean effect of -0.8 mmHg (He et al., 2015). Another lifestyle intervention study reported a significant reduction in BMI of students in the intervention group (-1.76kg/m2) whiles students in the control group showed an increase (1.13kg/m2) (Khumros, Vorayingyong, Suppapitiporn, Rattananupong, & Lohsoonthorn, 2019). A study showed significant reduction of smoking in the intervention arm as compared to the control arm (Gabrhelik et al., 2012). Another study reported that participants in the intervention group significantly increased consumption of fruits and vegetables when compared to the control group (Drapeau, Savard, Gallant, Nadeau, & Gagnon, 2016).

The main aim of this study is to evaluate the effectiveness of a school-based intervention programme on CVD risk factors which will be based on the Information- Motivation-Behavioral skills (IMB) model. Physical inactivity, smoking, alcohol, unhealthy diet, obesity, and hypertension will be the modifiable risk factors that will

be targeted for change among public secondary schools in the Brong Ahafo Region of Ghana.

**1.2 Problem Statement**

Cardiovascular disease (CVD) is the leading cause of death globally. The burden has been increasing in Ghana and has therefore become a major public health problem. In Ghana it is a leading cause of death since 2001 and has continued as one of the major causes of death since then. In 2008, cardiovascular diseases were responsible for

14.5% of all hospital deaths (Ghana MOH, 2012; GHS, 2015).

Despite all the CVD preventive risk factor measures in place in Ghana, the risk factors among adults have shown increasing trends over the years (MOH, 2012; GHS, 2015). Also, because the risk factors for the development of CVDs begin in childhood and are carried into adulthood, there should be an urgent need to educate students on the risk factors of CVDs right from childhood. Again, CVDs can be prevented if interventions that reduces the risk factors of the diseases are made available to people (Mendis et al., 2011) and that addressing a single modifiable risk factor still leaves one at a higher risk of developing CVDs because of failure in tackling the other coexistent risk factors. Also merely educating students on healthy lifestyles without interventions by reducing CVD risk factors may not be enough.

Therefore, to reduce this health and economic burden of the disease in Ghana, the prevalence of the disease and its risk factors among the youth and adults must be reduced drastically. In order to achieve this, preventive measures must start as soon as possible among students in schools in the country. This is because school health programs have shown to result in consistent improvement on the general health status of students. Two districts (Kintampo-North and Nkoranza-North districts) in the region were then selected for this study. This is because the educational levels in the two districts are low and accessibility to health information is poor. In this study, to the best of our knowledge, no behavioral modification intervention studies to reduce CVD risk factors among secondary school students in Ghana has been carried out. Since behavioral change still remains a driving force for reducing CVDs, there is therefore an urgent need for a behavioral change prevention intervention among secondary school students.

The IMB model is one of such psychological conceptualization for understanding and promoting health-related behavior. The IMB conceptualizations was developed (Fisher & Fisher, 1992) to address limitations found in other related theories. This included description of relationship among constructs, predictive validity of key constructs, conceptual parsimony and the inclusion of constructs that are needed for understanding and changing health behaviors. It was also designed to make it easy to be translated into other intervention programs such as addressing obesity-related behaviors, adherence to complex medication regimens, HIV preventive behaviors, and safety gear

utilization behaviors, among others (Fisher & Fisher, 2000; Fisher, Fisher, & Harman, 2003).

**1.3 Significance of Study**

This study will contribute to the body of knowledge on CVD risk factors among the secondary school students in the Brong Ahafo region of Ghana. Again, the intervention module if successful, can be adapted and incorporated by the Ghanaian Ministry of Education (MOE) into the school curricula program. Furthermore, the intervention study will inform, motivate, and give students the necessary skills that will enable them to practice healthy lifestyle behaviors such as doing at least 60 minutes moderate to vigorous physical activities daily, consumption of healthy foods such as fruits, vegetables, and seafood whilst reducing sugar and salt intake, as well as quitting or not initiating smoking and alcohol.

The IMB is a very powerful behavioral change tool that has been used over the years to improve and to sustain healthy lifestyle behaviors (Chang, Choi, Kim, & Song,

2014). The model had the potential in reducing CVD risk factors because is it composed of critical elements that were needed to adopt and maintain healthy behaviors. The constructs are based on social and health psychology theories that was developed to address limitations in social and health psychology theories such as the description of relationship among constructs, predictive validity of constructs, and the inclusion of constructs that are needed for understanding, changing, and sustaining healthy behaviors.

Also on sustainability of the intervention, students will be trained not to only reduce CVD risk factors alone, but to act as peer educators among their friends and in the home. This study will involve the participation of teachers and school authorities. Physical Education (PE) teachers will be trained by the researchers to implement the physical activity module during PE lessons while the other teachers will be trained on the health education module for continuous implementation after the intervention.

**1.4 Research Question**

The research question of this study is: what are the effects of the behavioral modification intervention program in reducing cardiovascular disease risk factors among secondary school students?

**1.5 Objectives of the Study**

**1.5.1 General Objective**

The general objective of this study is to develop, implement and evaluate the effectiveness of a behavioral modification intervention program to reduce cardiovascular disease risk factors among secondary school students in Brong Ahafo, Ghana.

**1.5.2 Specific Objectives**

The specific objectives of this study are:

1. To determine and compare the socio-demographic characteristics among intervention and control groups at baseline.

2. To determine and compare knowledge, motivation, behavioral skills and CVD risk factors (physical inactivity, smoking, alcohol consumption, unhealthy diet, BMI, diastolic and systolic blood pressures) between intervention and control groups at baseline.

3. To develop and implement a behavioral modification intervention program to reduce CVD risk factors among secondary school students in Brong Ahafo, Ghana.

4. To evaluate the effectiveness of behavioral modification intervention program to increase knowledge, motivation and behavioral skill on CVD risk factors between intervention group as compared to control groups at six months post intervention and also within groups from baseline to six months.

5. To evaluate the effectiveness of behavioral modification intervention program to reduce CVD risk factors in intervention group as compared to control group at six months and also within groups from baseline to six months among secondary school students in Brong Ahafo.

**1.6 Research Hypotheses**

The research hypotheses of this study are:

1. There will be no difference in the socio-demographic characteristics between the intervention and control groups at baseline.

2. The behavioral modification intervention program will be effective in improving the knowledge of CVD and its risk factors, motivation, and behavioral skill score among the participants in the intervention group as compared to control group and also within the groups from baseline to six months among secondary school students in Brong Ahafo, Ghana.

3. The behavioral modification intervention program will be effective in promoting physical activity levels of participants in the intervention group as compared to control group and also within the groups from baseline to six months among secondary school students in Brong Ahafo, Ghana.

4. The behavioral modification intervention program will be effective in reducing the prevalence of smoking among participants in the intervention group as compared to control group and also within the groups from baseline to six months among secondary school students in Brong Ahafo, Ghana.

5. The behavioral modification intervention program will be effective in reducing the prevalence of alcohol consumption of participants in the intervention group as compared to control group and also within the groups from baseline to six months among secondary school students in Brong Ahafo, Ghana.

6. The behavioral modification intervention program will be effective in promoting fruits and vegetable intake among participants in the intervention group as compared to control group and also within the groups from baseline to six months among secondary school students in Brong Ahafo, Ghana.

7. The behavioral modification intervention program will be effective in increasing seafood and water intake and reducing carbohydrates, fats and oils, fried eggs, fried chicken, carbonated drinks, plain sugar, sweet snack, and salted fish intake among participants in the intervention group compared to control group and also within the groups from baseline to six months among secondary school students in Brong Ahafo, Ghana.

8. The behavioral modification intervention program will be effective in reducing body weight and BMI of participants in the intervention group as compared to control group and also within the groups from baseline to six months among secondary school students in Brong Ahafo, Ghana.

9. The behavioral modification intervention program will be effective in reducing the mean diastolic and systolic blood pressures among participants in the intervention group as compared to control group and also within the groups from baseline to six months among secondary school students in Brong Ahafo, Ghana.

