**Figure 2.2 : Conceptual Framework**

**CHAPTER 3**

**METHODOLOGY**

**3.1 Study Location**

Ghana is located on the West Coast of Africa and has a total land area of 238, 537 square kilometer. Ghana has a population of 24,658,823 (Ghana Statistical Service (GSS), 2012). The official language is English. Akan, Ga, Ewe and Dagbani are the most widely spoken local languages in the country. The country is divided into ten administrative regions namely Greater Accra, Ashanti, Brong Ahafo, Central, Eastern, Northern, Upper East, Upper West, Volta, and Western in Figure 3.1.

Located in mid-Ghana, Brong Ahafo (BA) region has 16.6% and 9.4% (males: 49.6% and female: 50.4%) of the total land area and population of Ghana respectively. The region has an average growth rate of 2.2% and a tropical climate with temperatures averaging 24oC and a double pattern rainfall. The region has two main vegetation which are the moist semi-deciduous forest and the savanna woodland. The region serves as a transit point for travelers from the south to northern part of the country. Agriculture is the main economic activity in the region. Adult literacy rate in the region is 44.6% (55.4% illiterate) while the youth is 61.5% and the predominant ethnic group in the region is Akan out of over ten ethnic groups. There are about 57 secondary schools in the region which are spread across 29 districts. Two (2) districts were selected for this study and each of the districts had two public secondary schools and all were included in this study. These were Kintampo North Municipality and Nkoranza North District. The Kintampo North has 4.1% of the total population of the region. Males constitute 49.6% as compared to females who are 50.4%. The population in the municipality is mainly youthful as 42.4% are under 15 years and 60 years and above are only 6.1% (GSS, 2013). The Nkoranza North district on the other hand has 2.9% of the region’s population. The males (50.5%) in the district are slightly higher than their female counterparts (49.5%). Likewise in Kintampo North, a higher percentage (41.3%) of the population are under 15 years whereas a smaller number,

7.1% are 60 years and above. The age range of secondary school students in Ghana is from 14 to 19 years olD.

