**3.4.2.1 Inclusion Criteria**

The inclusion criteria into this study will be all public secondary school students in Kintampo North and Nkoranza North districts, Brong Ahafo region.

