**3.15.2 Dependent Variables**

The dependent variables of this study are sub divided into primary and secondary outcomes. There were;

i. The primary outcomes are CVD knowledge and its risk factors, motivation, behavioral skills, physical activity, smoking, alcohol consumption, and dietary intake.

ii. The secondary outcomes are body weight, BMI, diastolic and systolic blood pressures.

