**3.16 Operational Definition of Terms**

**3.16.1 Body Mass Index**

Weight in kilograms (kg) and height in meters (cm) were measured to determine BMI calculated as weight in kilograms divided by the square of height in meters (kg/m2). Subjects will be classified based on mean BMI for age and gender for children and adolescents. Adolescents were categorized into four groups which were underweight, normal weight, overweight, and obese with cut off points of <5th, 5th to < 85th, 85th to < 95th and ≥95th percentiles of the WHO standard respectively (Barlow, 2007; WHO, 2007).

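### Hypothesis 8 counts a within-group fall in raw weight and BMI as success in growing, mostly non-overweight students, and no six-month test uses the protocol's own BMI-for-age classes

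*Protocol*

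**What the plan says.** Hypothesis 8 (Protocol, 1.6) reads "The behavioral modification intervention program will be effective in reducing body weight and BMI of participants in the intervention group" and continues "as compared to control group and also within the groups from baseline to six months". It therefore has two parts: a comparison with control, and a before-after change inside each group. The abstract states the same direction without restricting it to heavier students: "The study is also expected to reduce weight, BMI, smoking and alcohol habits of the intervention group".

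The outcomes are continuous: "The secondary outcomes are body weight, BMI, diastolic and systolic blood pressures" (3.15.2). Section 3.17.3 analyses them at six months with independent t-tests between groups, paired t-tests within groups, a mixed-design ANOVA and a GLMM. The abstract says the GLMM includes group, time and group-by-time terms.

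Entry is not limited by weight: "The inclusion criteria into this study will be all public secondary school students in Kintampo North and Nkoranza North districts, Brong Ahafo region" (3.4.2.1). On age, section 3.1 says "The age range of secondary school students in Ghana is from 14 to 19 years", which is a description and not an eligibility limit.

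Section 3.16.1 recognises that BMI at these ages has to be read against age and sex: "Subjects will be classified based on mean BMI for age and gender for children and adolescents". It defines four percentile classes, including underweight. In section 3.17.3, BMI appears under chi-square only for the baseline comparison. The categorical tests named at six months cover smoking and alcohol only.

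**The concern.** There are two separate difficulties.

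1. **Growth.** Some of these students are still gaining height and weight. A before-after change in raw kilograms, and possibly in kg/m2, mixes growth with any programme effect. Under the within-group part of hypothesis 8, a programme that holds gain below what would otherwise have happened can appear ineffective.

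2. **Direction.** The risk factor the protocol sets out to change is obesity (1.1). Most students are not overweight, yet a lower mean is read as benefit whoever loses the weight. Loss in an underweight student moves the result toward success, and no planned six-month test would show it, although the class that would reveal it is already defined.

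At stake is the interpretation of two secondary outcomes: a wrong conclusion from the within-group tests, and a between-arm mean that cannot distinguish less overweight from thinner thin students.

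**Working it through.** The protocol gives no power or target effect for weight or BMI, so there is no stated figure to reproduce.

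**Share not overweight**
- National survey (1.1): it "reported that 8% of the students were either overweight or obese", so 100 - 8 = 92% are not.
- Table 2.2 (2.6.5), obesity plus overweight: 4.4 + 10.3 = 14.7%, 0.8 + 12.2 = 13.0%, 2.9 + 11.7 = 14.6%. Not overweight: 85.3%, 87.0%, 85.4%.
- If the overweight column already includes obesity, the Table 2.2 values become 89.7%, 87.8% and 88.3%, still within 85% to 92%.
- Of the 848 students (3.11): 848 x 0.08 = 68 to 848 x 0.147 = 125 are overweight or obese, leaving about 723 to 780 who are not.

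**What the mean reflects**
- If only overweight students lost weight, a 0.5 kg fall in the overall mean would need an average loss among them of 0.5 / 0.147 = 3.4 kg to 0.5 / 0.08 = 6.3 kg.
- If each of them lost 1 kg/m2 (assumed), the overall mean would fall by 0.08 to 0.15 kg/m2.

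**Growth and the two comparisons**
Let g be the six-month growth common to both arms and d the size of the programme's reduction. Neither is in the protocol. Assume g = 0 to 2 kg and d = 0.5 or 1.0 kg.
- Within intervention: g - d. Within control: g. Between arms: (g - d) - g = -d.

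| g (kg) | Within intervention, d = 0.5 | Within intervention, d = 1.0 | Between arms |
|---|---|---|---|
| 0 | -0.5 | -1.0 | -0.5 or -1.0 |
| 0.5 | 0.0 | -0.5 | same |
| 1.0 | +0.5 | 0.0 | same |
| 2.0 | +1.5 | +1.0 | same |

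Once growth reaches the size of the effect, the within-group change is zero or positive although the programme works. The between-arm difference does not move.

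Raw weight is more exposed than BMI. At a constant BMI of 20, growing from 160 to 161 cm (assumed) adds 20 x (1.61² - 1.60²) = 20 x 0.0321 = 0.64 kg with no change in BMI.

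Growth need not be large to decide the paired test. With 424 students per arm, an assumed SD of change of 1 kg/m2, and students treated as independent, the standard error is 1 / √424 = 0.049. A growth-only BMI rise of 0.1 kg/m2 then gives z = 0.1 / 0.049 = 2.06.

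**The case against.** **The randomised comparison is sound as regards shared growth.** A reader might infer from hypothesis 8 that normal growth counts as failure of the endpoint as a whole. The text does not support that. The hypothesis also compares with control, and section 3.17.3 gives the GLMM the task of determining overall effectiveness. Common growth cancels there, and gaining less than control counts as success. This stands, and confines the growth problem to the within-group part.

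**The within-group wording is not specific to BMI.** It recurs in hypotheses 2 to 9. True, but weight is where a rise without treatment is to be expected, so the harm is most concrete here.

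**A fall in the mean need not come from thin students.** A reader might say it must, given 85% to 92% not overweight. That does not follow. The protocol cites -2.0 kg/m2 against control in overweight children (2.6.5). Applied to 8% to 14.7% of students, this alone gives a mean fall of 0.16 to 0.29 kg/m2. Those children were in a targeted programme, so this is an upper illustration, but it defeats the word must. What remains is that the mean cannot tell the two sources apart.

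**A z-score does not cure the direction problem.** This also stands: a mean z-score falls when a thin student loses weight. It helps with age and sex, not with who benefits.

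**Age and gender are already listed as confounders (3.15.3).** The model form is not fixed and may be in a SAP not seen here, so it cannot be said that adjustment will fail. With two schools per arm, a difference in age or sex mix would be chance imbalance, not systematic bias.

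**A six-month test on the classes could also be in the SAP.** Possibly, but the direction and the within-group criterion are fixed in the protocol itself.

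**Conclusion.** The point holds in limited form. The within-group part of hypothesis 8, with its paired tests on raw weight and BMI, is confounded with growth and can give the wrong answer as written: under the assumed values, a true -0.5 kg effect appears as anything from -0.5 to +1.5 kg. The between-arm and group-by-time contrasts are not affected by growth common to both arms.

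The direction problem affects both parts. On the protocol's figures 85% to 92% of students are not overweight, a lower mean credits loss in normal-weight and underweight students, and the classes in section 3.16.1 are named in no six-month test. How much this would distort the result cannot be computed, because the protocol gives no underweight prevalence.

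The 85% to 92% rests on document figures alone. The growth, effect and SD values are assumptions used to show the mechanism. Weight and BMI are secondary outcomes and nothing is powered on them, so this is an inexpensive correction and not a threat to the trial's main conclusions.

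**What to change.** - Restate hypothesis 8 as a between-arm comparison of change in weight and BMI. Drop within-group reduction as a success criterion for these two outcomes; within-arm changes can be reported descriptively.
- Add a six-month between-arm comparison of the proportion overweight or obese, using the section 3.16.1 classes.
- Report, by arm, the number of students who move into the underweight class.
- Report BMI-for-age-and-sex z-score, on the WHO reference cited in 3.16.1, beside raw BMI, to handle age or sex differences between the four schools. It should accompany the class comparisons and not replace them. Making it the sole scale is more debatable, since several trials and reviews the protocol cites report raw BMI.

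Cost: protocol wording and one or two derived variables. Date of birth, gender, weight and height are already on the Appendix A questionnaire. The downside is that a binary overweight-or-obese outcome has less power than the mean, so it should be read with its interval and not as a stand-alone test.
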